## 8.3 Statistical Software

All data summaries and listings were performed using appropriate software as specified by the statistician (e.g., STATA)

## 9 Demographic and Baseline Characteristics

Demographic and baseline characteristics will be tabulated (see Appendix 1). In addition, if available, individual risks for non-breast-cancer morbidity and mortality will be compared [e.g. age, height, weight].

## 10 Outcomes

### Completeness

- 1.1 A patient is considered to have complete follow up if they **are dead or withdrawn**. “Withdrawn” means the patient has withdrawn consent for further follow-up information to be collected.
- 1.2 A patient is considered as having **recent follow up** if their status is known within 1 year before the reference date for completeness (2 May 2018),
- 1.3 Completeness is assessed at 3 time points
  - 1.3.1 5-years – the usual time to report
  - 1.3.2 10-years – protocol specifies at least 10 year follow up of every patient.

Thus, a patient is considered to have

**5-year complete follow up** if they have at least 5 years of follow up or have a recent follow up or are dead/withdrawn – this was 93.5% at the time of the last publication

**8-year complete follow up** if they have at least 8 years of follow up or have a recent follow up or are dead/withdrawn

**10-year complete follow up** if they have at least 10 years of follow up or have a recent follow up or are dead/withdrawn

Completeness is judged by the following criteria by the TSC

1. Proportion with complete follow up should be high in each stratum
2. Patients’ death is a major cause of not attending the clinic – and hence absence of status of follow up. Therefore, the mortality rate of a centres/countries should be similar to that of the gold standard centres as it would mean that the follow up is complete -

RD = reference date for completion of follow up, nominally 02/05/2018

N5 = number of patients with at least five years of follow-up (from date of randomisation).

N8 = number of patients with at least eight years of follow-up (from date of randomisation).

$N_{10}$  = number of patients with at least ten years of follow-up (from date of randomisation).

$N_1$  = number of patients seen within previous 58 weeks (1 y plus 6 week window) of Reference Date

$N_f$  = include if  $N_{5/8/10}$  or  $N_1$ , the number of patients with adequate follow-up

$D_{all}$  = number of patients randomised (3451)

$D_{cens}$  = number of patients dead or withdrawn before 5 years

The median follow-up will be determined on the population:  $D_{all}$  and  $(D_{all} - D_{cens})$

**Survival without local recurrence** – the number alive without local recurrence (as 1 above) (censored=last date known to be alive or withdrawn)

**Local recurrence in the conserved breast:** Histologically or cytologically proven recurrence of tumour in the index breast. (censored=last date known to be alive, withdrawn, or dead)

**Index quadrant recurrence:** Local recurrence as in 1 above in the index quadrant. (censored=last date known to be alive, withdrawn, dead, other quadrant recurrence)

**Scar recurrence:** Local recurrence as in 1 above within 1cm of the scar. (censored=last date known to be alive, withdrawn, dead, non-scar recurrence)

**Other quadrant recurrence:** Local recurrence as in 1 above in other quadrants. (censored=last date known to be alive, withdrawn, dead, index quadrant recurrences)

**Invasive local recurrence in the conserved breast:** As in 1 above, excluding those with only in-situ disease. (censored=last date known to be alive, dead, withdrawn)

**Survival without invasive local recurrence:** As in 2 above, excluding those with in-situ disease (censored=last date known to be alive, withdrawn, any other type of relapse)

**Isolated local recurrence in the conserved breast:** As in 1 above, excluding those with distant disease within 3 months of local recurrence. (censored=last date known to be alive, dead, withdrawn)

**Survival without isolated local recurrence:** As in 2 above, excluding those with distant disease within 3 months of local recurrence. (censored=last date known to be alive, withdrawn, any other type of relapse)

**Overall survival:** The time interval between randomisation and death. (censored=last date known to be alive or withdrawn)

**Breast cancer survival:** The time interval between randomisation and breast cancer death (censored=last date known to be alive or withdrawn)

**Non-Breast-cancer survival:** The time interval between randomisation and non-breast-cancer death (also, cardiac and other cancer deaths separately) (censored=last date known to be alive or withdrawn)

Lung cancer and heart disease deaths (if possible as a subset analysis in smokers) and effect of laterality on non-breast cancer deaths [appendix], and correlation with EBRT dose.

**Disease free survival:** The time interval between randomisation and any type of breast cancer relapse or any death (censored=last date known to be alive, withdrawn)

Toxicity of surgery and radiotherapy as previously described.

Analysis for all outcomes of the original (Lancet 2010) cohort of the first 2232 patients (mature cohort) as well as of the first 1222 patients (earliest cohort) who be expected to have completed a median follow up of 10 years. The following will be regarded as EXPLORATORY ANALYSES

**Regional recurrence:** Recurrence in the axilla or supraclavicular fossa

**Axillary recurrence with distant disease:** Recurrence in axilla concurrent with distant disease, or within 3 months of diagnosis of distant disease, or after diagnosis of distant disease.

To assess if there is adequate follow-up: The ratios of both  $N_f / (D_{all} - D_{cens}) > 95\%$  as well as  $N_f / D_{all} > 95\%$  will be used. If we find that this is impossible after adequate effort, we will have to reconsider the boundary with Trial Steering Committee.

Checks will be made for bias in follow-up by randomised treatment and/or by centre and statistical models will be used to assess the effect of such a bias. Additional analyses, tables and figures may be produced including analyses to assist in the determination of outliers, unusual data from specific centres or subgroups, skewness, kurtosis, etc. at the discretion of the Trial Statistician. Inclusion of such analyses, tables in the final report is optional. In addition, planned subgroup analyses will be performed for the main end points: local recurrence, local-recurrence-free survival, overall survival, breast cancer survival and non-breast-cancer survival for patients who are PgR positive vs. PgR negative and ER receptor positive vs. ER receptor negative, method of diagnosis (screening vs symptomatic), use of hormone therapy, and other predictive/prognostic factors.

A cox- proportional hazard model will be used for analysis of any other predictive factors including variables such as age, tumour size, grade, HER2 status, axillary nodal involvement, vascular invasion, margin, whether screen detected or not. Influence of factors such as ASTRO and/or ESTRO criteria, timing of 1st surgery/biopsy in terms of menstrual cycle, time of the day of delivery of radiotherapy, height, weight, bra size, surgical technique and size of applicator used for TARGIT, dose prescription used for TARGIT, fractionation regime for EBRT, delay between initial surgery and delivery of TARGIT in the postpathology stratum, centre and country, use of systemic therapy, or other factors will also be explored provided sufficient data is available. Significant factors will be reported with absolute differences, and/or hazard ratios and 95%CI.

We shall also perform all the analysis for the first 1222 and 2322 patients recruited in the trial, referred to as the Earliest and Mature cohorts in the 2013/14 Lancet publication. We shall also perform these analyses for the first n number of patients in the pre-pathology stratum to enable a comparison with other trials of partial breast irradiation, where n matches the number of patients in those trials.

We shall describe completeness of follow-up, mastectomy rates, proportion of patients suspected and investigated to have local recurrence in each randomised arm, treatment of local recurrence, number of uncontrolled local recurrence at the time of death and use of EBRT in presence of high risk factors and the effect of radiation fractionation on toxicity. For completion, we shall analyse the cancer, toxicity, overall survival and non-breast-cancer survival outcomes as per treatment received (those that received only TARGIT, both TARGIT and EBRT and EBRT only), however, the results of these artificially created groups need to be interpreted with the consideration that TARGIT treatment is only recommended within a risk-adapted approach.

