In the name of probity and transparency we will conduct the statistical analyses in the ways we’ve published in the past but promote the importance of absolute numbers (not relative risks), and emphasise the actual values for the outcomes in each of the randomised arms, that matter to the patient and facilitate their decision-making process. The patient needs to know her chance of being alive without local recurrence – so local recurrence free survival is the relevant statistic, rather than the estimate of local recurrence calculated after censoring patients at the point of their death - which would give the artificial estimate as if patients live forever.

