#### **7.2 Recording of recurrence/new malignancies**

Recurrence includes any new occurrence of breast cancer apart from new disease in the opposite breast in the absence of previous recurrence (which is classified as a contralateral breast cancer). Local recurrence, for the purposes of this protocol, is defined as recurrence in the index quadrant of the breast. Loco-regional recurrence is defined as recurrence either in the ipsilateral breast (other than the index quadrant) or in the axilla. Ipsilateral supraclavicular and intramammary node recurrence are not classified as local recurrence since the prognosis of patients with recurrence at these sites is more similar to distant than loco-regional disease.

Confirmation of ipsilateral recurrence must be by histology or unequivocal cytology. Clinical examination and imaging are not sufficient. Careful recording of the site of the recurrence is required to determine whether it is at the site of the original tumour and/or within the treatment field to determine whether the disease is 'local' or 'loco-regional'.

Recurrence at any other site must be confirmed by appropriate imaging and/or biopsy. Details of both first loco-regional (breast and axilla) and first distant recurrence are required as well as the status of the patient with regard to active disease when treatment for local disease has been completed.

Development of new malignancy (including the contralateral breast) must be reported on the case report forms once a diagnosis has been confirmed.

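### Survival without invasive or isolated local recurrence is censored at other relapse, so deaths after a recorded relapse are not counted and the estimate is too high

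*Combined protocol and SAP*

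**What the plan says.** All the definitions are in SAP section 10 (Outcomes).

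- **Parent endpoint, survival without local recurrence:** "the number alive without local recurrence (as 1 above) (censored=last date known to be alive or withdrawn". Local recurrence and death are events, and only end of follow-up or withdrawal censors.
- **Survival without invasive local recurrence**, defined by reference to the parent: "As in 2 above, excluding those with in-situ disease (censored=last date known to be alive, withdrawn, any other type of relapse".
- **Survival without isolated local recurrence**, likewise: "excluding those with distant disease within 3 months of local recurrence. (censored=last date known to be alive, withdrawn, any other type of relapse".
- **The paired recurrence-only endpoint, invasive local recurrence:** "As in 1 above, excluding those with only in-situ disease. (censored=last date known to be alive, dead, withdrawn". Here death censors and other relapse does not.
- **Disease-free survival**, for contrast: "The time interval between randomisation and any type of breast cancer relapse or any death (censored=last date known to be alive, withdrawn".

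The item numbers behind the cross-references do not appear in the text. The only sensible referent for item 2 is the parent endpoint.

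SAP section 8.1 gives the reason for preferring a survival-type endpoint: censoring women at death yields a figure "which would give the artificial estimate as if patients live forever". Protocol section 7.2 makes the date of other relapse available: "Details of both first loco-regional (breast and axilla) and first distant recurrence are required as well as the status of the patient".

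**The concern.** Each of the two derived endpoints should differ from its parent in one respect only, namely which local recurrences count. As written they also differ in who stays at risk. A regional or distant relapse ends follow-up for the endpoint, and so does an in-situ local recurrence in the invasive version. A death after that date is then lost.

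Kaplan-Meier estimation assumes that women censored at a given time have the same outlook as those still followed. Distant relapse breaks that assumption badly, because it is a main route to breast-cancer death. The result is not the probability of being alive without the stated recurrence, and it cannot be compared with the parent. Section 8.1 objects to censoring at death; censoring at metastasis, shortly before death, has much the same effect. A difference between arms in distant relapse, with the deaths that follow, would be largely hidden in these two analyses.

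**Working it through.** **Step 1. Follow one patient.** A woman has a recorded distant relapse at year 2, dies at year 4 and never has a local recurrence.

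- Parent endpoint: event at year 4.
- Disease-free survival: event at year 2.
- Overall survival: event at year 4.
- Survival without invasive or isolated local recurrence, as written: censored at year 2, never an event.

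Nothing in the SAP explains the extra censoring or brings her death back in. The plan states no figure for these endpoints, so there is none to reproduce.

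**Step 2. Size, as an illustration.** Every rate here is an assumption, because the documents give none for distant relapse or death. Times are exponential and independent. Assumed 5-year net risks are invasive local recurrence 2%, other-cause death 3%, and distant relapse 2%, 4% or 8%. Median survival after distant relapse is 2 years. A fraction q = 10% of breast-cancer deaths has no recorded earlier relapse. In-situ and regional relapse are not modelled.

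Yearly hazards, from −ln(1 − risk)/5 and ln 2/2:

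- local recurrence a = 0.00404
- other-cause death b = 0.00609
- distant relapse d = 0.00816 (at 4%)
- death after distant relapse m = 0.34657

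Probability of no breast-cancer death by time t:
S(t) = [m·exp(−dt) − d·exp(−mt)]/(m − d), with density f(t) = −S′(t).

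At 4% distant relapse and 5 years, S(5) = (0.34657 × 0.96 − 0.00816 × 0.17678)/0.33841 = 0.9789. Then:

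- Overall survival = 0.97 × 0.9789 = 94.95%.
- Parent rule = 0.98 × 94.95% = 93.05%.
- Rule as written, if every breast-cancer death follows a recorded relapse (q = 0) = 0.98 × 0.97 = 95.06%, whatever the distant-relapse rate.
- Rule as written with q = 10%: the Kaplan-Meier hazard is a + b + q·f(t)/[(1 − q)·exp(−dt) + q·S(t)]. Integrated over 5 years, this gives 94.85%.

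Results with q = 10% (differences taken before rounding):

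| Years | Distant relapse at 5 years | As written | Parent rule | Inflation (points) | Overall survival | First-event deaths lost |
|---|---|---|---|---|---|---|
| 5 | 2% | 94.96% | 94.06% | 0.90 | 95.98% | 23.5% |
| 5 | 4% | 94.85% | 93.05% | 1.80 | 94.95% | 37.5% |
| 5 | 8% | 94.64% | 91.03% | 3.61 | 92.88% | 53.5% |
| 10 | 2% | 90.10% | 87.78% | 2.32 | 91.40% | 29.3% |
| 10 | 4% | 89.83% | 85.22% | 4.61 | 88.73% | 44.6% |
| 10 | 8% | 89.25% | 80.21% | 9.05 | 83.51% | 60.2% |

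The last column is the share of deaths from any cause, in women without earlier local recurrence, that the rule drops. A simulation of 2 million patients per scenario gives the same survival figures to within about 0.1 point.

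**Step 3. Two readings of the table.** Being alive without local recurrence cannot be more likely than being alive. Yet the as-written figure exceeds overall survival at 10 years with 4% distant relapse (89.83% against 88.73%) and at 5 years with 8% (94.64% against 92.88%). It also hardly moves as distant relapse goes from 2% to 8% (94.96% to 94.64% at 5 years), while the parent falls by 3 points.

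**Step 4. Sensitivity to recording.** At 4% distant relapse and 5 years, if 100%, 90%, 75% or 50% of breast-cancer deaths follow a recorded relapse, the inflation is 2.0, 1.8, 1.5 or 1.0 points. The share of first-event breast-cancer deaths lost equals the recorded share.

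**The case against.** **A narrower reading of the censoring item.** The quadrant and scar endpoints in the same section are censored at the complementary kind of local recurrence. Read that way, other relapse would mean only in-situ, or non-isolated, local recurrence, and metastasis alone would not censor. This is arguable, and the SAP does not define the term. But the disease-free survival definition speaks of any type of breast cancer relapse in the broad sense, and the matching recurrence-only endpoints carry no such item. Even the narrow reading censors women whose local recurrence comes with distant disease, before they die. It would shrink the effect but not remove the inconsistency.

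**Standing of the endpoints.** Neither is in the main objective (SAP 7.1), the listed secondary objectives (7.2) or the main end points named for subgroup analysis (section 10). This stands and limits the weight of the point. They are not labelled exploratory, though, as that label comes after their definitions, and the version history puts emphasis on all primary and secondary endpoints.

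**What a reader might infer beyond this.**
- *That the figure promised to patients is biased.* It is not. Section 8.1 names local recurrence free survival, the parent endpoint, and section 8.2 commits to reporting it by arm.
- *That an effect on distant relapse would go unseen in the trial.* It would not. Disease-free, overall and breast cancer survival would capture it.
- *That most breast-cancer deaths disappear.* The documents give no such figure. It holds only if more than half of those deaths follow a recorded relapse, which is plausible given protocol section 7.2 but not established.
- *That patients are removed because of later findings.* The wording "As in 2 above, excluding those with distant disease within 3 months of local recurrence" reads more naturally as defining an isolated recurrence. It needs clarifying but is not a demonstrated error.

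**Conclusion.** The point holds for these two endpoints. On the natural reading the censoring list contradicts the parent endpoint and the SAP's own reason for using a survival measure, and it biases the estimate upwards. That direction needs only that relapse raises the risk of death.

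The size is an illustration: about 0.9 to 3.6 points at 5 years, with about 24% to 54% of first-event deaths lost. It rests on the assumed rates, exponential times, the broad reading of other relapse, and 90% of breast-cancer deaths following a recorded relapse.

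The primary endpoint, overall survival, breast cancer survival and disease-free survival keep their own definitions and are unaffected. It should be fixed before the analysis, but it does not threaten the trial's main results. How the separate causes of death are estimated is a different question, and this point gives no ground for changing it.

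**What to change.** 1. Delete the other-relapse item from both censoring lists, so that they match the parent endpoint: last date known to be alive, or withdrawal.
2. State the event as the first of invasive (or isolated) ipsilateral breast recurrence or death from any cause. Other relapses are neither events nor reasons to censor.
3. State that the exclusion wording means that the recurrence is not counted as an event. The patient stays in the analysis and at risk.
4. Name the endpoints that the cross-references point to, in place of bare item numbers.

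If a relapse-censored quantity was intended, it needs another name and a stated reason, and should not be presented as survival.

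The cost is a few words in two definitions and one clarifying sentence. The data already collected suffice. Only the derivation of the two event indicators and dates changes.

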## 8.2 Methodology

The two arms of the trial will be compared on the basis of 'intention to treat': The methods below have been used in the previous analysis

1. Non-inferiority will be tested using the difference in binomial proportions of local recurrence in the first 5 years and its 90% confidence interval using standard methods.
2. We shall also test for any difference in survival function using the log-rank test and Wilcoxon tests, and Kaplan-Meier curves and proportional hazard regression models will be used to account for time-to event and censoring of the data; however, these shall not be used for testing non-inferiority.
3. We shall also use the integrated difference of the two survival functions to quantify the difference between the Kaplan-Meier curves for local recurrence and local recurrence free survival
4. In order to reduce the assumption of normal distribution in the above models, we shall also use the recently described method of restricted mean survival time approach for analysis of all outcomes

For the primary end point of survival without local recurrence, given the difficulties in understanding the concept of non-inferiority and the criticism that the 2.5% margin may be considered arbitrary, we will describe the main results in terms of the absolute number of events as well as 5-year Kaplan-Meier estimate (and its 95% CI) of local recurrence and local recurrence free survival for each of the randomised arms of the trial.

For the analysis of overall survival, breast cancer survival and non-cancer survival, we shall report the absolute number of events, 5-year KM estimate as well as the analyses to test the null hypothesis of equality.

Statistical significance will be defined as per the current alpha spend. If p values are used, then, for local recurrence statistical significance will be at  $p < 0.001$  (using the Lan-DeMets spending function method) (it was 0.01 at the last analysis), and for survival it will be  $p < 0.025$  (it was 0.05 at the last analysis).

We shall also consider performing these analyses using the Bayesian methods using meaningful priors from previous analyses.

We shall transparently display the results of all analysis.

The baseline comparisons between the two groups will be done using chi-squared test for categorical variables and independent two sample t-test for all continuous variables.

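### Kaplan-Meier estimates that censor competing deaths slightly overstate the absolute risks of cause-specific death and local recurrence; cumulative incidence should be reported and the rule for competing deaths stated

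*Combined protocol and SAP*

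**What the plan says.** SAP section 8.2 sets the estimator for the survival endpoints: "For the analysis of overall survival, breast cancer survival and non-cancer survival, we shall report the absolute number of events, 5-year KM estimate", together with tests of equality. It also plans a 5-year KM estimate, by arm, of local recurrence and of local-recurrence-free survival. No cumulative incidence function or other competing-risk method is named anywhere in the SAP.

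SAP section 10 defines the endpoints as follows:
- Breast cancer survival is given as "The time interval between randomisation and breast cancer death (censored=last date known to be alive or withdrawn"; a death from another cause is not mentioned.
- Non-breast-cancer survival is given as "The time interval between randomisation and non-breast-cancer death (also, cardiac and other cancer deaths separately) (censored=last date known to be alive or withdrawn"; here a breast cancer death is not mentioned.
- Overall survival counts any death and is given as "The time interval between randomisation and death. (censored=last date known to be alive or withdrawn".
- Local recurrence has the rule "censored=last date known to be alive, withdrawn, or dead", so here death is named as a censoring reason.
- Index-quadrant recurrence is given as "Local recurrence as in 1 above in the index quadrant", with death and recurrence in another quadrant both censored. Other-quadrant recurrence mirrors this.

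SAP section 8.1 explains why local-recurrence-free survival is preferred, "rather than the estimate of local recurrence calculated after censoring patients at the point of their death - which would give the artificial estimate". It also commits the report to absolute figures that help the patient decide.

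**The concern.** Death from another cause does not hide a later breast cancer death; it rules it out. KM treats the censored patient as still able to have the event, so one minus KM estimates the risk in a setting where the competing cause does not exist. It is not the share of patients expected to die of breast cancer.

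Section 7.2 lists breast cancer and non-breast-cancer survival as the parts of overall survival, so a reader will expect the two risks to add up to all-cause mortality. They will not. Section 8.1 makes this criticism of local recurrence estimates, and its reasoning carries over to cause-specific death.

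What is at stake is the accuracy of the absolute risks given to patients. The error grows with follow-up. Section 8.2 fixes only the 5-year estimate, but section 3 sets a 10-year completeness target and section 10 plans all outcomes in an early cohort with an expected median follow-up of 10 years. Section 10 also splits off cardiac and other-cancer deaths, which adds further competing causes. The restricted mean survival times planned for all outcomes would be computed from the same curves.

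**Working it through.** **1. Is a competing death censored?** For breast cancer survival, a death from another cause is not the defined event. The patient must therefore leave the risk set at some point, and the only rule given is the last date known to be alive, which in effect is the date of death. Keeping the patient at risk beyond death would contradict that rule. Censoring is the only workable reading, but it is inferred: the local recurrence list names death and the cause-specific lists do not.

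**2. Inputs.** The documents give no cause-specific death rates, so the plan has no figure of its own to reproduce. Assumed constant hazards per year, as a range:
- lower: h1 = 0.005 (breast cancer), h2 = 0.006 (other causes)
- upper: h1 = 0.010, h2 = 0.012

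**3. Formulas.**
- One minus KM with the other cause censored: K1 = 1 − exp(−h1·t), K2 = 1 − exp(−h2·t)
- Cumulative incidence: F1 = h1/(h1+h2) × [1 − exp(−(h1+h2)·t)]
- All-cause mortality: A = 1 − exp(−(h1+h2)·t) = 1 − (1−K1)(1−K2)
- Hence K1 + K2 − A = K1 × K2. The two KM survival curves multiply to overall survival, but the risks do not add.

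**4. Breast cancer death.**

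| Hazards | Time | 1 − KM | Cumulative incidence | Overstatement |
|---|---|---|---|---|
| lower | 5 years | 2.47% | 2.43% | 0.04 points |
| upper | 5 years | 4.88% | 4.73% | 0.14 points |
| lower | 10 years | 4.88% | 4.73% | 0.14 points |
| upper | 10 years | 9.52% | 8.98% | 0.54 points |

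For example, in the last row 1 − exp(−0.10) = 9.52%, and (0.010/0.022) × [1 − exp(−0.22)] = 0.4545 × 19.75% = 8.98%. Overstatements are taken from unrounded values.

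**5. Additivity.**
- 5 years, lower: 2.47% + 2.96% = 5.42% (unrounded sum) against A = 5.35%; excess 0.07 points.
- 5 years, upper: 4.88% + 5.82% = 10.70% against A = 10.42%; excess 0.28 points.
- 10 years, upper: 9.52% + 11.31% = 20.8% against A = 19.7%; excess 1.08 points, which is 9.52% × 11.31%.

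**6. Simulation check.** With n = 3451 (the number randomised in SAP section 10), 200 runs, uniform censoring between 6 and 18 years, and true 10-year risks of 5% and 10%, the mean KM risks were 5.30% and 10.27% against all-cause mortality of 15.03%, an excess of 0.545 points. The Aalen-Johansen risks summed to all-cause mortality with no gap.

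**7. Effect on the comparison of arms.** Give both arms the same breast cancer hazard (1 − KM of 2.0% at 5 years) and let 1 − KM for non-breast-cancer death be 1.5% in one arm and 3.5% in the other. The cumulative incidences of breast cancer death are then 1.985% and 1.965%, a difference of 0.02 points. With 5% breast cancer risk and 5% v 10% non-breast-cancer risk at 10 years, they are 4.875% and 4.748%, a difference of 0.13 points.

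**8. Local recurrence.** The same formula applies, with death before recurrence as the competing event, and the direction is the same.

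**The case against.** Much of the case on the other side stands.

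- **The plan does not condemn its own method by name.** A reader might infer that the SAP calls its cause-specific estimates artificial. It does not: the remark "which would give the artificial estimate as if patients live forever" is made of local recurrence only. Extending it to cause-specific death is sound reasoning, but it is the reviewer's step.
- **Section 10 does not say that competing deaths are censored.** That is inferred for the cause-specific endpoints. The defect visible on the page is an unstated rule.
- **Local recurrence is partly dealt with already.** Section 8.2 makes survival without local recurrence the primary endpoint and reports local-recurrence-free survival by arm. Non-inferiority is tested on binomial proportions, and section 8.2 excludes KM from that test. What remains is that the 5-year KM estimate of local recurrence is still reported with deaths censored.
- **Site components.** Section 8.2 sets no 5-year KM estimate for index-quadrant or other-quadrant recurrence, so the point reaches them only if time-specific risks are shown.
- **The tests are not invalid.** A reader might infer that the survival comparisons are biased. Log-rank and Cox analyses that censor competing deaths are valid for cause-specific hazards. Event counts are also reported, and these add up if the cause categories cover all deaths.
- **The size at 5 years is very small.** The larger figures belong to 10 years, where section 8.2 fixes no KM estimate. The upper hazards imply about 10.4% all-cause mortality at 5 years, and nothing in the documents shows this to be realistic for tumours of good prognosis.

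None of this removes the core point: the stated estimator does not give the absolute risk that section 8.1 says patients need, and a standard one does.

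**Conclusion.** The concern holds as a minor defect of estimation. The direction is certain once competing deaths are censored and both hazards are above zero. The size rests on assumed constant hazards, because the documents supply no death rates: about 0.04 to 0.14 points for breast cancer death at the one fixed time point of 5 years, and 0.14 to 0.54 points at 10 years. In the illustration, the distortion between arms at 5 years is 0.02 points. The documents do not support a claim that any planned test, significance level or conclusion on the primary endpoint would change.

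A separate wording problem bears on additivity under any estimator. Section 8.2 speaks of non-cancer survival, while section 10 speaks of non-breast-cancer survival and includes deaths from other cancers. If the section 8.2 label were taken literally, deaths from other cancers would fall into neither reported category.

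**What to change.** 1. State in SAP section 10, for each cause-specific endpoint, how a death from another cause is treated.
2. In section 8.2, report Aalen-Johansen cumulative incidence by arm, with the difference and its 95% CI, for breast cancer death, non-breast-cancer death and local recurrence. Do the same for the site components, and for cardiac and other-cancer deaths, if time-specific risks are reported for them.
3. Keep the log-rank and Cox analyses, labelled as cause-specific.
4. Use one term for deaths not due to breast cancer in sections 8.2 and 10, so that the categories cover all deaths.

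The cost is a few sentences of SAP text and slight extra analysis in standard software. The new estimates will be less directly comparable with the earlier KM reports; showing the KM figures alongside deals with that.
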